### Sample size

For our primary analysis, assuming a two-sided α error of 0.05, a T2:non-T2 event ratio of 1:1 and a mean±SD population difference in δ FEV_1_ of 10±10%, n=46 will provide 90% of power to detect the difference in our primary outcome on an unpaired two-sample t-test. According to a recent Canadian study that assessed the proportion of randomly selected adults with physician-diagnosed asthma who fulfil objective criteria to confirm the diagnosis of asthma, 18.3% of participants reporting a severe asthma attack in the past year (11 of 60) did not have asthma confirmed.^61^ We thus conservatively estimate that 20% of patients recruited will not count towards the n=50 needed for the primary analysis.

Including a cohort of 12 healthy control participants, each assessed during a single visit, is intended to enhance our ability to relativise demographics, lung function and inflammatory measurements observed in the study. Recruitment will continue until the target number of confirmed asthmatics and healthy controls has completed the study.

We acknowledge that the secondary and exploratory analyses will likely be underpowered and view these as exploratory but feasible within the proposed timeline of a pilot study serving to plan further clinical trials. Any significant finding for secondary and exploratory outcomes will require further confirmatory studies to support them.^62^

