#### Secondary outcomes

Change in ACQ-5 between visits according to type 2 inflammatory status.The proportion of patients who achieve a minimal clinically important difference (MCID) ≥10% for FEV_1_ and ≥0.5 points for ACQ-5, according to the presence of type 2 high or type 2 low events.^58^ The magnitude of response will be rated as poor, moderate or good if the change is <1×, ≥1× or ≥2× the MCID values, respectively.

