### Statistical analyses

Descriptive statistics will be presented for the complete sample and separated by groups (ie, frequencies and percentages for categorical, mean, and SD or median and IQR based on the distribution). The normality of variables will be assessed visually using Q–Q plots and histograms. Demographics will be compared between asthmatics and healthy controls using unpaired Student’s t-tests (Mann-Whitney) for continuous variables and Χ^2^ (Fisher’s exact test) for categorical variables. Due to the small sample size, no imputation methods are planned a priori for missing data. Frequencies and percentages of missing will be presented, and listwise deletion will be used for concerned analyses.

We will employ an unpaired two-sample t-test (Mann-Whitney U test if non-parametric) to assess the change in FEV_1_ (primary outcome) and ACQ-5 (key secondary outcome) between visits 1 and 2 according to type 2 inflammatory status. Additionally, to assess whether the observed change in FEV_1_ within subgroups defined by type 2 high events is clinically meaningful, we will employ a Χ^2^ test to compare the proportion of patients achieving the MCID between the two groups, using an MCID of 10% relative change in FEV_1_ and 0.5 points in ACQ-5. Finally, the above results will allow for a power calculation to plan a randomised controlled trial on key outcomes.

Exploratory analyses will include an association of the outcome measures with type 2 inflammatory mediators at visit 1 using further multivariable models. To consider the influence of potentially confounding variables, simple and multiple linear regression models will be performed for both independent variables (BEC and FeNO). Covariates considered are age, sex at birth, body mass index, atopic status, serum IgE, Asian race, nasal polyposis,^21^ smoking history, Charlson index, treatment intensity at baseline, exacerbation history in the past 12 months and ACQ-5. Only confounders associated (p<0.1) with FEV_1_ will be included in the final multivariable model. A linear mixed-effects analysis of the longitudinal improvements in parameters measured at home (FeNO, peak expiratory flows and symptom scores) according to baseline FeNO and BEC.

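### The visit 1-to-visit 2 comparisons are complete-case analyses with non-completers replaced, and no stated analysis covers patients lost through deterioration

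*Protocol article*

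**What the plan says.** Three parts of the protocol article act together.

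- **Statistical analyses.** No imputation is planned, with small sample size given as the reason. The amount of missing data will be reported, and "listwise deletion will be used for concerned analyses". The FEV1 and ACQ-5 comparisons are of changes from visit 1 to visit 2, and the MCID comparison is built on the same changes.
- **Sample size.** "Recruitment will continue until the target number of confirmed asthmatics and healthy controls has completed the study". The only loss allowed for is unconfirmed asthma: "We thus conservatively estimate that 20% of patients recruited will not count towards the n=50 needed for the primary analysis". No figure is given for dropout or a missed visit 2. The text does not say whether completion means visit 2 or the later follow-up contact.
- **Primary outcome.** Type 2 status is set from visit 1 eosinophils and FeNO, so it is known even for a patient who never returns.

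The sensitivity analyses that are described concern sex, gender and race. None concerns missing data.

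**The concern.** Participants enter during an attack and are reassessed after seven days of treatment. Someone who is admitted, or too unwell for spirometry on day 7, may have no visit 2 FEV1. Under listwise deletion that person leaves the mean change and the responder denominator, and recruitment continues until another completer takes the place. If such losses are related to response, response among those analysed is overstated. If they also differ between type 2 groups, the main contrast shifts. Meeting the recruitment target does not remove this, because it restores the number analysed and not the patients who were lost. The results are also meant to feed the power calculation for a randomised trial, so a bias would carry forward.

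**Working it through.** **1. The plan's own figure.** Inputs from Sample size: "assuming a two-sided α error of 0.05", "a T2:non-T2 event ratio of 1:1", a "population difference in δ FEV_1_ of 10±10" per cent (standardised effect 1.0), and the claim that "n=46 will provide 90% of power to detect the difference in our primary outcome on an unpaired two-sample t-test". By the noncentral t distribution, 23 per group gives 91.2% power and 22 per group gives 89.97%, so 46 is the smallest even total that reaches 90%. The sample-size arithmetic is sound.

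**2. What the completer target protects.** With equal groups and a 10-point difference, 50 completers give 93.4% power, 46 give 91.2% and 40 would give 86.9%. Replacement protects precision. It does nothing about bias.

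**3. Which analyses need visit 2.**

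| Analysis | Needs visit 2? |
|---|---|
| FEV1 change (primary) | Yes |
| ACQ-5 change (key secondary) | Yes |
| MCID proportions | Yes |
| Mixed model of home FeNO, peak flow and symptoms | No |
| Visit 1 demographics; visit 1 venous versus point-of-care eosinophils | No |

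**4. Scenario A: the poorest changes are lost.** Assumptions not in the documents: true mean change 5% (type 2 low) and 15% (type 2 high), SD 10%, and patients with a change below 0 miss visit 2 with probability p. Results are from simulation.

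| p | Lost, low / high | Completer difference | Low group reaching a 10-point gain | Power, 25 per group |
|---|---|---|---|---|
| 0 | 0% / 0% | 10.0 | 31% | 93% |
| 0.25 | 7.7% / 1.7% | 9.4 | 33% | 92% |
| 0.50 | 15.4% / 3.3% | 8.6 | 36% | 89% |
| 1.00 | 30.8% / 6.7% | 6.3 | 45% | 79% |

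With the cut-off at -5 instead of 0, the completer difference is 9.5, 9.0 or 7.7. The contrast shrinks because one common cut-off removes more of the type 2-low group.

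**5. Scenario B: a failing fraction f with mean change -10%.** If the true group mean is m, the completer mean is (m + 10f)/(1 - f).

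- Low group, m = 5: f = 0.10 gives 6.0/0.90 = 6.67; f = 0.20 gives 7.0/0.80 = 8.75.
- High group, m = 15: f = 0.10 gives 16.0/0.90 = 17.78; f = 0.20 gives 17.0/0.80 = 21.25.
- Loss in the low group only: the difference is 15 - 6.67 = 8.33 or 15 - 8.75 = 6.25.
- Equal loss in both groups: the difference is 17.78 - 6.67 = 11.1 or 21.25 - 8.75 = 12.5.
- No net change when 20% of the low group fail: (15 + 10g)/(1 - g) = 18.75 gives g = 3.75/28.75, about 13% of the high group.

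The contrast can therefore shrink, widen or stay put, depending on how loss differs between the groups.

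**6. MCID proportions.** Deleting two failures from 25 moves 10/25 (40%) to 10/23 (43.5%). From 10 it moves 4/10 (40%) to 4/8 (50%).

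**7. Does the fix work?** In Scenario A nobody who is lost reached the MCID. Counting them as not reaching it gives back the true low-group share: 0.334 × (1 - 0.077) = 0.308 and 0.364 × (1 - 0.154) = 0.308.

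**The case against.** The strongest case on the other side has four parts.

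- **Scope.** A reader might infer that every analysis is completers-only. That does not hold: deletion is limited to the analyses affected, and the home-monitoring model and visit 1 analyses do not need visit 2.
- **Mechanism.** A reader might infer that patients who deteriorate are replaced by patients who recovered. The documents do not support this. A replacement has to complete, not recover. No rule withdraws a patient who deteriorates, and a poor responder who attends day 7 stays in with a poor value. The recruitment sentence also has a good purpose, since asthma may be confirmed only after participation. Any bias comes from deletion under informative loss, not from replacement.
- **Direction.** A reader might infer that the contrast is pulled towards no difference. That needs heavier loss in the type 2-low group. The plan hypothesises a lesser response there, which is not the same as non-attendance, and Scenario B with equal loss goes the other way.
- **Already handled, or left elsewhere.** Missing frequencies will be reported, the secondary analyses are called exploratory, and an unseen analysis plan might add sensitivity analyses.

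The first three stand in full and set the limits of this point. The fourth stands in part. The article states a deletion rule for its primary analysis, so this is a stated choice and not merely an omitted detail. The promised missing-data counts are not specified by type 2 group or with reasons. Small numbers argue against model-based imputation, but counting a known deterioration as a non-response needs no model.

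**Conclusion.** The point holds for the primary FEV1 comparison, the ACQ-5 change and the MCID proportions. These are complete-case analyses with non-completers replaced, and they can be biased if loss before visit 2 is related to response. Size and direction are not known. Every magnitude above rests on assumed group means, failure rates and failure severity, because the article gives no dropout rate. If few patients miss visit 2, the effect is small: losing 7.7% and 1.7% in Scenario A moves the difference only from 10 to 9.4. This is a cheap improvement, not a flaw that invalidates the design.

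**What to change.** - Keep recruiting to the target number of completers, which protects FEV1 precision.
- Keep all confirmed patients classified at visit 1 in the MCID denominator, and count those who miss visit 2 because of deterioration as not reaching the MCID.
- Add one FEV1 sensitivity analysis giving these patients the worst rank. It fits the Mann-Whitney test that the article already names as its alternative.
- Report non-completion with reasons by type 2 group.

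The cost is a few sentences, a recorded reason for each missed visit 2, and one extra analysis. The downside is slightly more conservative responder rates. The target should not be redefined as patients enrolled, because that would give up the protection of the analysable number shown in step 2 of the working.

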## Discussion

The proposed observational and translational before/after pilot study of asthma attacks across the range of asthma severities will be the first to focus on the role of BEC and FeNO and explore the clinical and biological factors affecting OC treatment response in acute asthma. We view our pilot study of POC measurements for assessing type 2 inflammation and airway infection as a stepping stone to plan a clinical trial allowing for biomarker implementation in the primary care setting. Biomarker-guided management could avoid harm to individual patients and society stemming from inappropriate use of OCs and/or antibiotics.

We expect events identified by raised BEC and/or FeNO to benefit most from corticosteroids, and POC tests to be useful theragnostic and mechanistic tools. Specifically, we expect increased BEC and FeNO to predict greater improvements in (a) FEV_1_ (primary outcome), (b) ACQ-5 scores (key secondary outcome), and (c) inflammatory mediators, symptoms, and other physiological aspects (exploratory outcomes). If the study hypothesis is confirmed—a phenotypical variability in treatment responses associated with type 2 airway inflammation—then the utility of BEC and FeNO could be studied to manage asthma attacks in a randomised controlled trial.

Three distinct studies in asthma attacks are underway, each with its unique objectives. ExCluSie-F (Phenotyping and Classifying Asthma Exacerbations; NCT05304039) is a prospective cohort that will explore the association between phenotypical characteristics and a composite outcome of treatment effectiveness. On the other hand, ‘APEX’ (Asthma: Phenotyping Exacerbations; NCT04293588) is a longitudinal cohort with participants who have experienced at least one asthma exacerbation in the previous year that aims to assess the proportion of patients displaying eosinophilic and non-eosinophilic phenotypes. Lastly, ‘BOOST’ (Recovery of Breakthrough Asthma Attacks Treated with Oral Steroids While on Monoclonal Antibody Therapy) is a prospective observational study involving adults on long-term biological treatment for asthma that will compare clinical recovery between individuals with high FeNO levels during their asthma attacks and those with low FeNO.^63^

PRISMA (Phenotyping the Responses to Systemic Corticosteroids in the Management of Asthma Attacks) Study offers a distinctive and comprehensive perspective in asthma exacerbation research compared with the studies above, as it stands out by exploring the vital and often less-understood components of asthma exacerbation: their response to standard medications, the utility of BEC and FeNO in acute settings, and the potential role of microbial infections in exacerbation dynamics. PRISMA can also be viewed as instrumental in participating and/or launching further studies about asthma attacks—a new and exciting frontier for biological therapies (eg, BeNReX (NCT04102800134), ABRA (NCT04098718135)).

If the POC test results prove reliable and are also acceptable to patients and their primary care providers, the table will be set for a placebo-controlled trial, such as being done in chronic obstructive pulmonary disease.^64–66^

The main potential pitfall is the unknown proportion of type 2 high versus type 2 low events in our sample, which ranges from mild-to-severe asthma. In severe asthma, approximately 80% of exacerbations are type 2 high,^38^ whereas in mild-to-moderate asthma, the proportion is unknown yet expected to be lower.^19 20^ However, we have planned our primary analysis on continuous variables and thus estimate that we will be able to pick up a signal of biomarker-based variability in acute corticosteroid responsiveness. The second major pitfall is our reliance on FEV_1_ as the primary outcome variable: type 2 inflammation has not always been linked with different FEV_1_ values.^12 38^ Third, we anticipate many patients may reach out to us either after starting OCs or due to a lack of response to a recent course. To ensure the exclusion of volunteers who have recently taken OCs, we have established a requirement that participants should not have taken a dose within the last 48 hours. Although this exclusion criterion may lead to a bias towards recruiting individuals with less severe events, as those requiring immediate OCs will not be included, we expect that most participants will be recruited through our specialised asthma clinics, which will facilitate the inclusion of severe asthmatics and individuals with more severe airway events. A fourth important limitation is that this is an observational study with a relatively small target sample size; the former does not preclude interesting mechanistic signals from being observed, yet we acknowledge the latter.

We are mindful of the safety concerns associated with conducting sputum induction after the pandemic. As a mitigation strategy, we will use nasosorption as a surrogate measure for assessing airway compartment inflammation. Additionally, we plan to implement rapid COVID-19 molecular testing at the beginning of each study visit to ensure the safety of our staff and increase the likelihood of conducting sputum induction.

To conclude, we have planned a study which is, to the best of our knowledge, the first to assess the variability in response to acute systemic therapies (corticosteroids and/or antibiotics) in asthma according to the inflammatory and microbial phenotypes. We hope that by providing this nuanced understanding, we can contribute to guiding the design of future biomarker-stratified randomised controlled trials that will be more finely tuned to the needs of individual patients with asthma.

## Data Availability

Data sharing not applicable as no datasets generated and/or analysed for this study. Not applicable.
